#### Interim analysis

This analysis will be performed by an independent expert team to examine some relevant data as baseline, safety outcome, and efficacy outcome data to consider ending the study if no trend is observed

## Conclusions

Intranasal DXM at low doses could be a more effective therapeutic option to control peripheral and central inflammation during ARDS in severe and critical forms of SARS-CoV-2 infection. In addition, it could stabilize the activity of the HPA axis upon this severe stress condition. Although low-dose systemically administered DXM is beneficial for COVID-19 patients, it cannot reach effective therapeutic concentrations in the CNS to control neuroinflammation. In contrast, intranasal administration of DXM is highly effective in controlling neuroinflammation, as demonstrated in experimental inflammation models [41–44]. Therefore, in the REVIVAL trial clinical protocol, we propose boosting the effect of low-dose DXM treatment through an intranasal route of administration. This route will allow reaching the CNS at therapeutic doses that may effectively reduce the morbidity and mortality in severe or critical COVID-19 patients, further than that reported in the RECOVERY trial.

Low doses of intranasal DXM are currently being tested (clinicaltrials.gov id: NCT04513184) in a randomized study in hospitalized COVID-19 patients (moderate and severe forms). The clinical evolution and respiratory parameters of the patients receiving intranasal DXM (experimental treatment) are compared with those of patients receiving 6 mg of intravenous DXM, the currently recommended treatment (https://www.covid19treatmentguidelines.nih.gov/). Considering the prevalence of metabolic syndrome and obesity in Mexico, the therapeutic scheme has been weight-adjusted. A DXM dose of 0.12 mg/kg is administered for 3 days, followed by a dose of 0.06 mg/kg for 7 days. If the current approach yields fewer adverse effects and does reach the CNS to control neuroinflammation as we hypothesized, there will be direct interest to extend this protocol to several COVID hospitals of the National Health System in Mexico. In addition, increasing the initial sample size (preliminary results) will be required to publish the study and share it with the International scientific community.

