**Methods:**

This is an approved open-label, multicenter, randomized controlled trial to compare the effectiveness of intranasal versus intravenous dexamethasone administered in low doses to moderate and severe COVID-19 adult patients. The protocol is conducted in five health institutions in Mexico City. A total of 120 patients will be randomized into two groups (intravenous vs. intranasal) at a 1:1 ratio. Both groups will be treated with the corresponding dexamethasone scheme for 10 days. The primary outcome of the study will be clinical improvement, defined as a statistically significant reduction in the NEWS-2 score of patients with intranasal versus intravenous dexamethasone administration. The secondary outcome will be the reduction in mortality during hospitalization.

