#### Sample size and randomization

The analysts of the statistic team calculated the size with EPIDAT version 3.1.2 software, using the option “Sample size and surveillance curves” with an estimated 50% increase in the proportion of patients free of mechanical ventilation [intranasal DXM 70% vs. intravenous DXM 45%]. This value was estimated using the data of the COVID-19 patients registered in Mexican hospitals with a confidence of 95%, power of 80%, and proportion of losses of 10%. A sample size of 60 patients per group was obtained with these parameters. The randomization will be made with Sealed Envelope software. This software is freely available from https://www.sealedenvelope.com/simple-randomiser/v1/lists [Accessed May 5, 2020]. This study is a multicenter randomized controlled trial (Fig. 2).

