The internal random structure [$$ {L}^T\ {\hat{\varphi}}_AL $$] can change in different settings, but still will be a good approximation. Simulations studies showed adequate performance of modifications with different REML [60]. Finally, the structure of residual error will be analyzed within the lowest-level group. Once recognized, the covariance structure we will use unstructured, Toeplitz, or exponential corrections. This approach will give unbiased approximation even in presence of unbalanced samples.

The residuals for our mixed models will be considered by the source of present variability: The marginal residuals will predict the marginal errors, the conditional residuals, and the best linear unbiased predictor (BLUP) residuals. The conditional residuals will be standardized with:

$$ {\hat{\varepsilon}}_k^{\ast }=\frac{{\hat{\varepsilon}}_k}{\sigma\ \sqrt{p_{kk}}} $$ , where *p*_*kk*_ represents the *k*th element of the covariance structure. These residuals are functions of the joint leverage of fixed and random effects.

Subgroup analysis will be based on interaction as secondary analysis. This information will help to identify multiplicative effects from basal conditions like the presence of type 2 diabetes, obesity, hypertension, clinical history IECA medication, or other conditions.

All analysis will describe the number of patients with the outcome of interests, the treatment effect (mainly using eta squared), additive and multiplicative interactions with 95% confidence intervals, and the direction of the interaction (positive or negative) by specific subgroups. The analysis will be performed with Stata version 17.0 [StataCorp LLC College Station TX]. A statistical difference with *P* < 0.05 will be considered significant.

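### The article fixes the trial at 120 patients, yet its Conclusions say the initial sample must grow before publication, without saying how later patients and the single 0.05 threshold would be handled

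*Protocol article*

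**What the plan says.** **The size is fixed at 120.** The abstract's Methods paragraph states "A total of 120 patients will be randomized into two groups", and the Participants section gives the same total. The section Sample size and randomization derives it from assumed proportions free of mechanical ventilation ("intranasal DXM 70% vs. intravenous DXM 45" percent), "with a confidence of 95%, power of 80%, and proportion of losses of 10" percent, and concludes: "A sample size of 60 patients per group was obtained with these parameters".

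**The Conclusions describe something else.** Their last paragraph says that if the intranasal approach has fewer adverse effects and reaches the central nervous system as hypothesised, "there will be direct interest to extend this protocol to several COVID hospitals of the National Health System in Mexico". The next sentence, introduced as an addition, says that "increasing the initial sample size (preliminary results) will be required to publish the study".

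**One threshold is given.** The Statistical analysis section ends: "A statistical difference with *P* < 0.05 will be considered significant". It mentions no allowance for repeated analysis. The Trial design section describes the study as open-label. The Interim analysis section foresees a look at efficacy data, and the only consequence it names is possible termination when no trend appears.

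**The concern.** A powered sample size tells the reader when the primary analysis takes place and on whom. Here the sample-size section says it takes place at 120 patients. The Conclusions call the initial sample preliminary and require a larger one before publication. As written, the article does not settle which sample carries the primary test.

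Two things are at stake:

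- **Error rate.** If the final size is chosen after results are known, in an open-label trial with one unadjusted threshold, there may be two opportunities to claim success where the plan accounts for one.
- **Reporting.** Read literally, the randomised comparison in the planned 120 patients would not be published on its own, only after an enlargement whose size, timing and analysis are not given.

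**Working it through.** **1. The plan's own figure.** The inputs are 0.70 and 0.45 free of mechanical ventilation, two-sided 0.05 (sidedness is not stated, so this is an assumption) and 80% power. The mean proportion is (0.70 + 0.45)/2 = 0.575.

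n per group = [1.96·√(2·0.575·0.425) + 0.842·√(0.70·0.30 + 0.45·0.55)]² / (0.25)² = (1.370 + 0.569)² / 0.0625 ≈ 60.2

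This rounds up to 61; an arcsine formula gives 60. So 60 per group is the output of a power calculation for a complete trial, not a pilot size. (The two-sided figure reaches about 60 only before the 10% losses are added. That is a separate matter and plays no part here.)

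**2. The passages side by side.** The abstract, the Participants section and the sample-size section all say 120. The Conclusions say that the initial sample must be increased. They do not give the size of the increase, the event that triggers it, whether the first 120 are pooled with later patients, or whether a claim may be made at 120. Each of these is therefore an assumption below.

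**3. Set-up for the error rate.** Let z₁ be the test statistic on the first 120 patients and z₂ the statistic on all patients after enlargement by a fraction f. With no true difference, both are standard normal with correlation ρ = √(120/(120(1 + f))) = √(1/(1 + f)). Each test uses the limit 1.96.

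**4. A claim allowed at either analysis, with the trial always enlarged.** The error rate is P(|z₁| > 1.96 or |z₂| > 1.96):

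| Enlargement f | Total N | ρ | Error rate |
|---|---|---|---|
| 25% | 150 | 0.894 | 7.1% |
| 50% | 180 | 0.816 | 7.7% |
| 100% | 240 | 0.707 | 8.3% |
| 200% | 360 | 0.577 | 8.8% |

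**5. Significant results claimed at 120; only favourable non-significant results (0 < z₁ ≤ 1.96) enlarged and retested at 0.05.** The error rate is 5% plus the probability that such a trial becomes significant on the pooled data:

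| Enlargement f | Added, favourable direction | Added, unfavourable direction | Error rate |
|---|---|---|---|
| 50% | 1.35% | under 0.01% | 6.4% |
| 100% | 1.62% | 0.03% | 6.7% |
| 200% | 1.78% | 0.13% | 6.9% |

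**6. One test only.** If the trial is always enlarged and tested once on the pooled data, the error rate is 5.0%. It is also 5.0% overall, two-sided, if results with z₁ > 0 lead to enlargement and a single pooled test, and all other results lead to a single test at 120.

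**7. Enlargement only after a significant result at 120.** If a claim at 120 stands, enlargement adds nothing to 5%, because every enlarged trial has already made its claim. If pooled significance is also required, the rate in the favourable direction is 0.6% to 1.2%, against a nominal 2.5% (f from 200% to 50%).

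The interim look is not included in any of these figures.

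**The case against.** **The sentence may mean early data growing towards 120.** Recruitment was under way, and the Data Availability section calls the work a first approach to a trial just started. On that reading nothing is enlarged. It is possible, but it fits poorly: the sentence speaks of the initial sample size, and the one before it concerns taking this same protocol to further hospitals.

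**A reader might infer that the sample grows only after a favourable primary result, so that the pooled estimate carries forward a chance excess.** The article does not support this. The conditional clause governs interest in extending to other hospitals, and it rests on adverse effects and central nervous system effect, not on the NEWS-2 outcome. The sample-size sentence is added to it and has no clear condition of its own.

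**A reader might infer that unfavourable results would go unpublished.** This does not follow either. Publication is tied to a larger sample, not to the direction of the result, and the Data management section speaks of publishing global results without such a condition.

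**A reader might infer that the plan necessarily exceeds 5%.** It does not. Pooling and double testing are nowhere stated, a separate follow-on study is also compatible with the text, and steps 6 and 7 show rules that stay at or below the nominal level.

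**It is a loose closing remark, and error control for an extension belongs in the full protocol or analysis plan.** The details could indeed sit there. But the point is not that detail is missing. The article makes a positive statement that conflicts with its own powered sample size.

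**Conclusion.** The point holds as an inconsistency with conditional consequences. The article gives 120 as the planned sample in three places and in its Conclusions requires a larger one before publication. This needs no assumption beyond the natural reading of the sentence. The same is true of the literal condition placed on publishing the 120-patient comparison.

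The size of the error-rate problem cannot be fixed from the document. It ranges from none (5% with one test), through about 6.4% to 6.9% (favourable non-significant results enlarged by 50% to 200%), to about 7% to 9% (a claim allowed at both analyses, enlargement of 25% to 200%). These figures assume two-sided tests at 0.05, pooling of all patients, and enlargement sizes that the article does not give.

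It deserves correction before results are known, because a rule for enlargement written after open-label data have been seen would carry little weight.

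**What to change.** Reconcile the Conclusions with Sample size and randomization by replacing the sentence on increasing the sample. The new text should state that:

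1. the analysis of the 120 randomised patients is the final primary analysis of this trial and will be published whatever its result;
2. any extension to other hospitals is either a separate trial with its own primary analysis, into which the first 120 are not pooled for the test, or follows an enlargement rule with type I error control, fixed before any outcome data are seen. Such a rule must state the size of the increase, what triggers it, and how the 0.05 is shared between the analyses.

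Under the first option the cost is a change of wording; the sponsor gives up only unplanned pooling of the first 120 patients into a later test. The second option keeps pooling available, but the rule must be written now, and the threshold at one or both analyses will normally be stricter than 0.05.

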## Data Availability

Data and materials are not available at this moment, because the work being considered is the first approach to a clinical trial currently started. When the study will be completed, the dataset obtained and analyzed will be available from the corresponding author only by reasonable request.

## Abbreviations

COVID-19: Coronavirus disease 19
CNS: Central nervous system
GCs: Glucocorticoids
NEWS-2: National Early Warning Score-2
COFEPRIS: Comisión Federal para la Protección contra Riesgos Sanitarios
SARS-CoV-2: Severe acute respiratory syndrome coronavirus 2
RNA: Ribonucleic acid
GFAP: Glial fibrillary acidic protein
NfL: Neurofilament light protein
PAMPs: Pathogen-associated molecular patterns
DAMPs: Damage-associated molecular patterns
ACE2: Angiotensin-Converting Enzyme 2
TMPRSS2: Transmembrane Serine Protease 2
NRP-1: Neuropilin -1
TLR: Toll-like receptor
IL-1β: Interleukin-1β
TNFα: Tumor Necrosis Factor α
ROS: Reactive oxygen species
P2X7: Purinergic Receptor P2X7
DVC: Dorsal vagal complex
NTS: Nucleus Tractus solitary
HPA: Hypothalamic-pituitary-adrenal
RVM: Rostral ventrolateral medulla
ACTH: Adrenocorticotrophic hormone
NF-κB: Nuclear Factor Kappa-Light-Chain-Enhancer of activated B cells
AP-1: Activating Protein-1
ATP: Adenosine Triphosphate
NLRP3: NLR Family Pyrin Domain Containing 3
DXM: Dexamethasone
BBB: Blood-brain barrier
RBD: Receptor-binding domain
NETs: Neutrophils extracelullar traps
ARDS: Acute respiratory distress syndrome
CO-RADS: Coronavirus-19 Reporting and Data System
RT-PCR: Reverse transcription polymerase chain reaction
AIDS: Acquired immunodecficiency syndrome
CRF: Case report format
HGMEL: Hospital General de México [name]
